#### Sample size of cases

The sample size of 4100 study participants anticipated in the intervention arm (Ife North LGA) will include both asymptomatic (40–70 years) and symptomatic (30–70 years) women that will undergo screening and diagnostic evaluations respectively. In any screening exercise, there will be symptomatic cases that will use the opportunity of screening to present for evaluation. We anticipate a CDR of at least 3.5%. This expectation is supported by our previous publication of a mixed screening and diagnostic population in this geographic region demonstrating a breast CDR of 3.5% [19]. The CDR in this study will be the number of cancers detected among all study participants, including both the symptomatic and screening arms.

Our previous data demonstrate that the mean breast tumor size from an entirely symptomatic population at OAUTHC was 10.5 cm. This is much larger than findings from our recent study from the same region which included a screening population which demonstrated an average breast cancer size of 3.3 cm [19, 22]. We therefore project that cancers in the intervention community will be follow a similar pattern.

The primary outcome measure in this study is the stage at diagnosis. To achieve this, we projected the number of cases needed to detect a difference in the proportion of cases based on stage at diagnosis between the two study arms. From our preliminary data of 25 staged cancers, there were 7 (7/12, 58.3%) and 2 (2/13, 15.38%) stage IV cancers in the control and intervention arms respectively, with a 43% difference between the two groups. In order to detect a 43% difference in stage IV diagnoses between the two study arms with 80% statistical power at an alpha of 0.05, 23 cases will be needed in each arm. Our preliminary data show 13 total cancer cases detected in 791 patients and 12 total cancer cases detected in 82 patients in the intervention and control arms, respectively, in the first year. Going by this annual accrual rate, in two years, there should be 26 cancer cases out of 1582 patients in the intervention arm and 24 cancer cases out of 164 patients in the control arm. Therefore, achieving the 23 cases required for statistical significance in the stage at diagnosis in each arm at the end of the 2-year study period is possible.

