**Methods:**

The study (ClinicalTrials.gov identifier: NCT05321823) will adopt a randomized two group clinical trial design with one local government area (LGA) serving as an intervention arm and another serving as the control. Both LGAs will receive breast cancer awareness education but only one will receive the interventions. In the intervention arm, asymptomatic (40–70 years) and symptomatic (30–70 years) women will be invited for breast evaluation which will be performed by trained Community Health Nurses using Clinical Breast Exam (CBE), and iBE. Those with positive findings will proceed to imaging using mobile mammography and ultrasound brought to the LGA every month. Symptomatic women with negative findings on CBE and iBE will be scheduled for repeat clinical evaluation on a short-term basis (one month). The Radiologist will obtain core needle biopsies as indicated and transfer them for prompt pathological assessment. Women presenting to the Primary Healthcare Centers in the control LGA will be referred directly to Obafemi Awolowo University Teaching Hospitals Complex as per the current standard of care. Records of all breast cancer cases seen in the two LGAs during the study period will be obtained. The program metrics will include screening participation rate, cancer detection rate, stage at diagnosis, and timeline from detection to initiation of treatment. The stage at diagnosis and timeline from detection to treatment compared between the two LGAs will be used to assess the impact of the intervention. The study is proposed for 2 years; however, a descriptive analysis will be carried out at 1.5 years to evaluate the retention of the study participants.

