The 3 selected wards in Ife North LGA have an estimated total screening population (women 40–70 years) of 5,800 while the 2 selected wards in Ife East LGA have an estimated total screening population of 4,500. With an anticipated participation rate of about 70% (which is projected from the number of women willing to undergo CBE screening in a previous study in the same state [14]), we project that about 4,100 women will undergo breast evaluation in the intervention arm during the study period. The sample size of 4100 refers to the total number of patients to be accrued broadly in the intervention arm (Ife North LGA). Even though there have been three wards randomly selected in Ife North LGA and two wards randomly selected in Ife East LGA, we will assume that the rate of recruitment of patients will be the same in the randomly selected wards. In each study arm, the CDR is expected to be the same across the wards since they are expected to be similar in terms of health provider density and risk factor profile like genetic makeup, age at first-term pregnancy, parity, and family history of patients presenting for breast evaluation. Because we expect there to be no statistically significant differences in risk factors between the wards within each LGA, we do not incorporate any design effects in sample size calculation.

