#### Control arm

The control LGA is about 4 kilometers from OAUTHC which is the referral tertiary hospital in this study. There are radiological (including ultrasound, mammography, computerized tomography, and magnetic resonance imaging services), pathological and surgical specialty services for breast cancer within OAUTHC which is also the primary institution of the study’s principal and co-investigators in Nigeria. In the control LGA, awareness creation will follow a similar procedure as outlined above for the intervention LGA. No other intervention will take place in the control arm. Women will not be invited to participate in a screening program and there is no community-based imaging, biopsy, or navigation. Women are expected to present to the PHCs if they have breast complaints which is a routine practice. Management of patients with breast-related complaints will be based on the current standard of care which is a review by the CHNs who refer or clinically manage otherwise based on his/her assessment. Twice a month, research staff will visit the selected PHCs in the control LGA to obtain data on the number and records of breast-related cases seen at the PHCs and those referred to OAUTHC. Patients referred to OAUTHC for suspicion of breast cancer will be tracked to determine the stage at diagnosis and the timelines from presentation at the PHC to eventual treatment at OAUTHC. In addition, patients presenting directly to OAUTHC from the LGA based on self-referral will also be identified and their data obtained.

Although the control arm participants do not have intervention provided in their LGA, they however get same workup, management and are navigated along the same pathway as the intervention arm participants once they present in OAUTHC for screening and diagnostic evaluation.

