**Fig 4 pone.0284341.g004:**
[figure not shown]
Outcome measures in the control and intervention communities.

Primary outcome measures.

Stage at presentation: This will be determined using both clinical and radiological assessment to determine the TNM stage among those with histopathologically confirmed breast cancer. It is expected that the number of patients with late-stage disease may be high at the outset, but this is expected to reduce as screening progresses in the intervention arm. Therefore, besides the absolute number of cases per stage, the pattern of presentation over time will also be assessed to determine if there is a decline in the number of late-stage cases between the prevalence and incidence rounds of screening. Cases of breast cancer from the intervention and control arms will be tracked both at the PHCs and OAUTHC. The stage and pattern of presentation of cases from the two arms will be compared.

Secondary outcome measures.

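### The sizing for stage IV appears to use only programme attenders in the intervention arm, while the outcome is framed on all cases from both communities, so the 80% power assumes no intervention cases outside the programme

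*Protocol article*

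**What the plan says.** All references are to the protocol article.

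- **Sizing inputs (Sample size of cases).** The planning rates are given as "there were 7 (7/12, 58.3%) and 2 (2/13, 15.38%) stage IV cancers in the control and intervention arms respectively". From the 43-point difference the article concludes that "with 80% statistical power at an alpha of 0.05, 23 cases will be needed in each arm".
- **Source of those cases (same section).** The article reports "Our preliminary data show 13 total cancer cases detected in 791 patients and 12 total cancer cases detected in 82 patients". The first pair of figures is for intervention and the second for control, both from year one. Doubling them, it projects that "there should be 26 cancer cases out of 1582 patients in the intervention arm and 24 cancer cases out of 164 patients", the last pair again being control.
- **Population behind the attenders (Sample size of study participants).** "The 3 selected wards in Ife North LGA have an estimated total screening population (women 40–70 years) of 5,800". Participation of about 70%, or about 4,100 women, is planned.
- **What is to be compared.** The abstract's Methods paragraph says "Records of all breast cancer cases seen in the two LGAs during the study period will be obtained". The text on stage at presentation, under the primary outcome measures, says "Cases of breast cancer from the intervention and control arms will be tracked both at the PHCs and OAUTHC", and that stage will then be compared between the arms. The Aims place the impact at the level of the intervention LGA against the control LGA.
- **How cases are found.** For the control LGA, the Control arm section adds that "patients presenting directly to OAUTHC from the LGA based on self-referral will also be identified and their data obtained". The intervention-arm sections on evaluation, imaging and navigation follow only women who enter through the primary health centres (PHCs). They contain no matching sentence for Ife North residents who go straight to the hospital.

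**The concern.** The 13 intervention cancers are presented as the yield of 791 evaluated women. That count is then projected to 1,582 women, on the same footing as the 4,100 expected to be examined. The natural reading is that 2/13 is the stage IV rate among attenders. Cancers in women of the same wards who never attend still arise and still present, probably under usual care, and the sizing makes no allowance for them.

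Two readings are open, and each has a problem:

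- **Non-attender cases are counted**, as the abstract and the outcome text suggest. The intervention rate is then a mixture, and 15.4% is too favourable an input.
- **Non-attender cases are not counted.** The 23 then stands on its inputs. But women who chose to come are compared with control cases found by any route, including self-referral. A difference in stage could then reflect who attends rather than what the programme does for the community.

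At stake are the meaning of the primary contrast and a power figure with little room for dilution.

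**Working it through.** **1. Reproduce the plan's figure.** Inputs: control 7/12 = 58.3%, intervention 2/13 = 15.4%, difference 42.9 points, alpha 0.05 taken as two-sided (the article does not say), Fisher's exact test with power by full enumeration. With 22 per arm power is 78.6%; with 23 it is 81.4%. So 23 is the smallest size that reaches 80%, and the arithmetic is not in dispute.

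**2. Attendance on the article's own counts.** 791/5,800 = 13.6% in year one and 1,582/5,800 = 27.3% projected over two years, against 70% planned. The number projected never to attend is 5,800 − 1,582 = 4,218.

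**3. Dilution.** Let m be the number of intervention-community cases outside the programme over two years. Assume they are stage IV at the control rate. Then

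intervention rate = (26 × 2/13 + m × 7/12) / (26 + m)

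For m = 5: (4 + 2.917)/31 = 22.3%, a difference of 58.3 − 22.3 = 36.0 points. Exact two-sided Fisher power against 24 control cases:

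| m | Intervention cases | Stage IV rate | Difference (points) | Power |
|---|---|---|---|---|
| 0 | 26 | 15.4% | 42.9 | 88% |
| 3 | 29 | 19.8% | 38.5 | 80.5% |
| 4 | 30 | 21.1% | 37.2 | 75% |
| 5 | 31 | 22.3% | 36.0 | 76% |
| 10 | 36 | 27.3% | 31.0 | 61% |
| 20 | 46 | 34.1% | 24.3 | 48% |
| 26 | 52 | 36.9% | 21.5 | 39% |

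The small reversal between m = 4 and m = 5 comes from the discreteness of the exact test. Power falls below 80% at about four such cases.

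**4. What m might be.** The article gives no value. Two rough routes use its own figures:

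- Control yield over the whole intervention community: 24/4,500 × 5,800 = 30.9 cases in two years; less the 26 already projected, about 5 remain.
- The incidence in the Introduction: 52/100,000 × 4,218 × 2 = 4.4 cases.

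Both are soft. The first assumes that all control cases come from the two selected wards (4,500 women), although self-referrals are described as coming from the LGA. The second is a general incidence and would probably be higher at ages 40–70. Early detection of prevalent cases among attenders could also leave more than 5 outside the programme.

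**The case against.** The strongest objection is that the premise is inferred. The article speaks of total cancer cases in the intervention arm and never says that the 13 exclude women who presented directly at the hospital. It also says that cases from both arms are tracked there. That is fair, so the point is worded as what the text appears to say. The asymmetry remains: self-referral is spelled out for one arm only.

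A reader might infer from 27% attendance that most intervention-community cancers fall outside the programme, so that the true contrast is far below 43 points and the trial is unlikely to show it. The documents do not support that. Attendance among women is not coverage of cancers. The programme's yield was 13/791 = 1.6%, far above 52/100,000, and the article itself expects symptomatic women to use the screening to present.

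It is also tempting to apply the control yield to the 4,218 non-attenders alone: 24/4,500 × 4,218 = 22 cases. But this adds the full control yield to 26 cases already found, giving about 48, where the same yield over all 5,800 women implies about 31.

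Two further objections have force. The Discussion reports slow early recruitment followed by a surge, so attender cases may exceed 26; with 40 attender cases and m = 5, power against 24 controls is 86%. And if the primary set is limited to enrolled participants, the 23 is not wrong on its inputs; the difficulty is then self-selection, not sizing.

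The detailed wording of an analysis set can be left to an analysis plan. But the article itself describes case capture differently for the two arms and sizes on a population that appears narrower than the one it says it will compare, so the mismatch lies in what is stated.

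**Conclusion.** The point holds in conditional form. The 23 per arm is computed correctly, but its 80% power assumes that no intervention-community case outside the programme enters the comparison, and the article's outcome text points the other way. At the projected counts, three such cases leave power at about 80%. Five, the rough figure that the article's own rates suggest, give a 36-point difference and 76% power, a modest shortfall. Only a much larger number, 20 or more, brings power below 50%, and nothing in the documents establishes that.

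These figures rest on three assumptions: non-attender cases are stage IV at 58.3%; two-year accrual is 26 attender and 24 control cases; and the 13 preliminary cases are programme attenders. If non-attenders are left out instead, the power stands on its inputs, but the contrast is exposed to self-selection and unequal case-finding.

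**What to change.** 1. Define the primary case set in the same words for both arms: all histologically confirmed breast cancers newly diagnosed during the study in age-eligible residents of the selected wards, whether or not the woman attended a programme PHC.
2. Apply the hospital self-referral search, by residential address, to the Ife North wards as it is described for the control LGA.
3. Report attender-only cases as a secondary analysis, labelled as subject to self-selection.
4. In Sample size of cases, say whether the 13 preliminary cancers include any hospital presenters. State that the 80% assumes no intervention cases outside the programme, and give power over a range of m, for example 88% at 0, 76% at 5, 61% at 10 and 39% at 26.

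The cost is a change of wording, a less favourable stated power, and a modest record search that the abstract's promise to obtain all cases in both LGAs already implies.

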#### Sample size of community health nurses

To evaluate the projected 4,100 women over a year with approximately 220 working days, we estimate that a total of 19 examinations will be performed daily across the three selected PHCs in the intervention LGA. Three CHNs per facility (nine in total) will be trained to take focused breast history, perform the examinations (iBE and CBE), triage patients for imaging, and navigate patients through the referral pathway.

### Study participants

#### Inclusion criteria

Asymptomatic women 40–70 years of age and symptomatic women 30–70 years of age with breast-related symptoms will be included in the study.

#### Exclusion criteria

Women who live outside the selected intervention and control LGAs as well as women not meeting the age criteria. Women who are too sick to present to the PHCs on their own without support will be excluded from the study.

#### Consent

Written informed consent will be obtained by the trained CHNs from all eligible study participants after reading and understanding the participant information sheet attached to the consent form (S2 File). All questions and clarifications raised by the study participants will also be addressed by the trained CHNs.

#### Activities, approach, and intervention

The summary of the activities, approach, and intervention to be implemented is shown in Figs 1 and 2.

**Fig 1 pone.0284341.g001:**
[figure not shown]
SPIRIT schedule of enrolment, interventions, and assessments.

**Fig 2 pone.0284341.g002:**
[figure not shown]
Summary of project design and methods.

#### Groundwork

To guarantee broad acceptability and aid implementation, the first phase of the project entails interactions with the local district health authorities, traditional chiefs, women leaders, local health authorities, and other opinion leaders in the LGA. This research already has the support of the State Health Authorities who provided a letter of support for this project. Further consultation with the health authorities is aimed at designing an operational framework for the utilization of the primary health centres to ensure the successful integration of the screening program into the existing health system structure of the LGA. Meeting with the leaders and stakeholders is aimed at having a good understanding of the social factors that may impact the screening program, understanding the expectations of the people, and ensuring adequate community participation.

#### Baseline survey

A survey of women in the 2 LGAs (n = 163, each) will be conducted to assess baseline knowledge of breast cancer, screening practices, and perceptions about breast cancer before awareness creation and intervention. The survey instrument (S3 File) has a total of 8 sections consisting of thirty-one items. The first seven sections of the survey instrument were adopted from the validated AWACAN tool [23] while the eighth section (containing ten questions on awareness of breast cancer screening modalities and practices) was developed for this study. The English version of the survey instrument was translated into Yoruba language (the local language spoken in the selected LGAs in South-west Nigeria) and back to English language to ensure comparability. This was performed by a linguistic expert in the Department of Linguistics and African Languages of Obafemi Awolowo University (OAU), Ile Ife, Osun State, Nigeria.

The selection of women for the survey will be done using multistage sampling from the district to the street. Within each street, household sampling will be by convenience sampling of any available woman 40 years and older. The number of women sampled from each district will be proportional to the fraction of the population the district represents. Each LGA will be re-assessed with the same survey instrument (S3 File) at the end of the first year.

The CHNs will also be evaluated to assess their level of knowledge about breast cancer before intervention. This will be done both quantitatively and through qualitative interviews to understand potential cultural nuances and perceptions about breast cancer that need to be factored into the execution of the project.

#### Training staff in the intervention arm

Community Health Nurses (CHNs) in Nigeria are registered nurses and/or registered midwives with one-year post-basic training in community health nursing. They are trained to provide health education, conduct health screening, dispense medications, and administer immunization in addition to a variety of general nursing procedures like wound dressing, checking vital signs, antenatal care, and delivery, etc. Prior to this study, CHNs in the PHCs don’t have any core experience with breast cancer screening and treatment except in basic anatomy taught in nursing school and continuous nursing education seminars and training.

Three CHNs in the three selected PHCs (n = 9) will undergo a two-week training targeted at obtaining a focused breast history, performing a CBE, the use of the iBE device, counseling, and patient navigation. Training will be in the form of didactic lectures, with the use of a training manual specifically designed for this study with information derived from various sources, such as the World Health Organization training manual and materials from the American Cancer Society. Other modes of training will include role-playing, videos, and demonstrations. Training will involve education on the basics of breast cancer, such as breast cancer epidemiology, anatomy and physiology, common benign breast conditions, breast cancer risk factors, symptoms and signs, screening, diagnosis, and treatment. The health workers will be trained on how to obtain focused breast history from women presenting for evaluation. The focused history includes seven questions to assess recent breast asymmetry, breast lump, bloody nipple discharge, nipple deformity, breast skin changes, axillary swelling, and a family history of breast cancer.

Training on the performance of CBE starts with visual inspection for breast asymmetry, visible lumps, skin changes, oedema, nipple retraction, discharge, or axillary swelling while the woman is in an upright position with hands on her hips and in a supine position. Health workers will subsequently be taught how to palpate the breast using the pads of the fingers with overlapping circular movements while the woman is in an upright and then supine position with the ipsilateral arm overhead. The axillary examination will also be taught. CBE lectures will be followed by video sessions, after which the technique will be demonstrated on breast models.

Training on the use of the iBE device will be conducted following the manufacturer’s manual (UE Life Sciences Inc.) and led by one of the principal investigators of the study who has extensive experience with the device. Each health worker will be required to perform approximately 30 examinations with the iBE to achieve proficiency similar to our pilot study [19].

CBE and iBE will first be performed on models, then on volunteers. After each examination, there will be a debriefing, beginning with self-evaluation, then feedback from other trainees, and then feedback from the trainers. Training is expected to last for 2 weeks based on our previous studies which demonstrated 1–2 weeks is needed to train community breast health volunteers in these exams.

Training will also include other important components such as patient counseling, effective communication, and professional ethics, such as confidentiality and data management. After the training session, each trained health worker will give a health talk which will be evaluated by the trainers to demonstrate their ability to counsel and effectively communicate with patients.

